## Abstract

**Background:**

Hypertension is a risk factor for cardiovascular disease, and the prevalence of hypertension tends to increase with age. Current treatments for hypertension have adverse side effects and poor adherence. The purpose of this study is to evaluate the effects of moxibustion on blood pressure in individuals with pre- or stage I hypertension.

**Methods/design:**

Forty-five subjects with pre- or stage I hypertension will be randomized into three groups: treatment group A (2 times/week), treatment group B (3 times/week), and the control group (non-treated group). The inclusion criteria will be as follows: (1) aged between 19 and 65 years; (2) prehypertension or stage I hypertension (JNC 7, Seventh Report of the Joint National Committee on the Prevention, Detection, Evaluation, and Treatment of High Blood Pressure); (3) the participants are volunteers and written consent obtained.

The participants in the treatment group A will undergo indirect moxibustion 2 times per week for 4 weeks, and the participants in the treatment group B will undergo indirect moxibustion 3 times per week for 4 weeks. The participants in the control group (non-treated group) will maintain their current lifestyle, including diet and exercise. The use of antihypertensive medication is not permitted. The primary endpoint will be a change in patient blood pressure. The secondary endpoints will be the body mass index, lipid profile, EuroQol and Heart Rate Variability. The data will be analyzed with the Student’s t-test and analysis of variance (ANOVA) (*p* < 0.05).

**Discussion:**

The results of this study will help to establish the optimal approach for the care of adults with pre- or stage I hypertension.

**Trial registration:**

Clinical Research Information Service KCT0000469

## Background

Hypertension is an important risk factor for cardiovascular diseases including stroke, myocardial infarction, congestive heart failure, kidney disease, and peripheral vascular disease [1-3].

It is estimated that in 2025, 1.56 billion adults will have hypertension [4]. According to the Seventh Report of the Joint National Committee on the Prevention, Detection, Evaluation, and Treatment of High Blood Pressure(JNC-7), patients with a blood pressure of 120–139/80–89 mmHg have prehypertension [5]. A recent study demonstrated that people with prehypertension were more likely to develop hypertension than those with normal blood pressure over the 50-year follow-up period [6]. According to a longitudinal population-based US cohort study, prehypertension increases the risk of developing cardiovascular diseases [7]. The results of another study suggest that prehypertension increases the risk of myocardial infarction, stroke, cardioplegia, and cardiovascular death in women [8].

Moxibustion involves the application of ignited mugwort (*Artemisia vulgaris*) at acupoints or other specific parts of the body to treat or prevent diseases. This technique is typically used to treat and prevent cold syndrome, deficiency conditions and chronic diseases [9]. Moxibustion can cause tissue damage as a result of skin irritation or even skin burns due to the thermal stimulation, which is performed at various temperatures. The thermal stimulation can also cause inflammatory responses and vascular changes. According to the findings of previous studies of moxibustion, mediators such as histamine and substance P are secreted, and this process promotes angiectasis [10]. It seems that inflammatory reactions that affect vascular activity may ease various cardiovascular diseases, including hypertension [11].

There are few published randomized controlled trials (RCTs) concerning moxibustion treatment for prehypertension. A systematic review on the effects of moxibustion on hypertension revealed no evidence that moxibustion is beneficial to people with hypertension. However, the differences between specific and non-specific effects should be examined in a future study that includes appropriate control groups [11].

## Methods/design

### Aims of the study

The aims of this pilot study are to evaluate the effects of moxibustion on blood pressure in patients with pre- or stage I hypertension, to test the methods used and to calculate the sample size required for future randomized trials.

### Design

This study will be a prospective randomized controlled trial, and participants will be recruited from Woo-suk University Hospital using notices at the hospital and newspaper advertisements.

In this pilot clinical trial, patients with pre- or stage I hypertension will be analyzed to determine the safety and efficacy of moxibustion, and basic analysis will be performed on the results. The study participants will voluntarily sign clinical trial consent forms, and all examinations and tests will be performed according to the clinical trial plan. Eligible subjects will be chosen based on specific inclusion and exclusion criteria. Participants will be randomized before the first treatment. Forty-five subjects with pre- or stage I hypertension will be randomized into three groups: treatment group A (2 times/week), treatment group B (3 times/week), and the control group (non-treated group). During each moxibustion treatment, each acupoint will be treated five times. The treatment will continue for 4 weeks. The follow-up assessment is designed to evaluate the long-term effects of moxibustion. Upon completion of the 4-week-long treatment, follow-up tests will be conducted at weeks 8,12,16,20 and 24 after randomization (Figure 1).

**Figure 1 F1:**
[figure not shown]
Flowchart of the study design.

This study has been registered with the ‘Clinical Research Information Service,’ Republic of Korea, which is a registry in the WHO Registry Network (KCT0000469).

The systolic and diastolic blood pressures will be measured in the arm using an automatic blood pressure meter (HD-505, Jawon Medical Co, Kyungsan City, Korea). The subjects will be fitted with a BP cuff on both arms. A trained researcher will measure the blood pressure carefully in the arm with higher BP while the subject is in the seated position. The blood pressure will be measured three times after the subject has rested for at least 10 min. All BP measurements will be taken in a temperature-controlled room. The three measurements will be carried out at 5-min intervals. The mean of these three measurements will be used in the data analysis. The participants will be instructed not to drink caffeinated drinks such as coffee or tea and not to exercise, smoke or eat 2 h before the blood pressure test. In addition, they will be instructed to avoid drinking heavily the day before the test [12].

The practitioner has had more than 3 years of clinical experience since completing 6 years of study at the College of Korean Medicine and has received a Doctor of Korean Medicine.

### Randomization

This study is designed as a pilot study to calculate the appropriate sample size for future randomized clinical trials. Allowing for a 20% dropout rate, each group will include 15 participants, which is the minimum sample size necessary to evaluate the effect of moxibustion [13,14]. In this study, stratified randomization will be performed by classifying subjects into age and sex by an online centralized randomization service.

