### Participants

Inclusion criteria were as follows: (1) aged between 19 and 65 years; (2) pre- or stage I hypertension (JNC 7); (3) the participants are volunteers, and written consent was obtained.

Exclusion criteria were as follows: (1) taking medications to control blood pressure; (2) secondary hypertension; (3) history of cerebrovascular disease, cardiovascular disease, malignant tumors, kidney diseases, liver diseases, thyroid gland diseases, active tuberculosis, or other infectious diseases; (4) diabetic patients taking insulin or anti-diabetic medications; (5) drug or alcohol dependence; (6) taking hemorrhagic disease and anticoagulation medications (excluding aspirin); (7) receiving systemic steroid therapy or immunosuppressive therapy; (8) taking medications that could affect blood pressure such as central nervous system depressants or stimulants; (9) pregnancy or the possibility of pregnancy; (10) hypersensitivity reactions following moxibustion therapy; (11) received oriental medicine treatment related to hypertension in the past month; (12) participants deemed unsuitable for the trial, as judged by the person in charge of the clinical trial (Table 1).

**Table 1 T1:** Patient inclusion and exclusion criteria

**Inclusion criteria**		**Exclusion criteria**	
1.	Aged between 19 and 65 years	1.	Taking medications to control blood pressure
2.	Pre- or stage 1 hypertension (JNC 7)	2.	Secondary hypertension
	-Systolic blood pressure between 120 and 159 mmHg	3.	History of cerebrovascular disease, cardiovascular disease, malignant tumors, kidney diseases, liver diseases, thyroid gland diseases, active tuberculosis, or other infectious diseases
	- Diastolic blood pressure between 80 and 99 mmHg	4.	Diabetic patients taking insulin or anti-diabetic medications
3.	The participants are volunteers and written consent obtained	5.	Drug or alcohol dependence
		6.	Taking hemorrhagic disease and anticoagulation medications (excluding aspirin)
		7.	Receiving systemic steroid therapy or immunosuppressive therapy
		8.	Taking medications that could affect blood pressure such as central nervous system depressants or stimulants
		9.	Pregnancy or the possibility of pregnancy
		10.	Hypersensitivity reactions following moxibustion therapy
		11.	Received oriental medicine treatment related to hypertension in the past month
		12.	Participants deemed unsuitable for the trial, as judged by the person in charge of the clinical trial.

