### Statistical analysis

The results of the intention-to-treat (ITT) analysis will be used to assess the validity of the study as a whole. The per-protocol (PP) analysis results will be used as a reference. The ITT analysis will be used as the main safety assessment technique.

Continuous data will be represented by the average, standard deviation, minimum value, and maximum value, whereas categorical data will be represented by a frequency table. For the comparison of the results among the groups, the analysis of variance (ANOVA) test will be used when the data are normally distributed; the Kruskal-Wallis test will be used otherwise. In addition, the chi-square test will be performed for categorical data.

After 4 weeks, the differences in systolic and diastolic pressure will be summarized for each group using descriptive statistics, including the median, average, standard deviation, and interquartile range. In addition, we will evaluate the effectiveness of the treatment using an analysis of covariance as the dependent variable, the baseline score as the covariate, the group as the fixed factor, and the hypertension stage as the stratified variable. In addition, we will compare the results for the stratified groups with the results for the whole subject pool (non-stratified) to determine whether hypertension stage is a suitable stratification variable. The differences in the systolic pressure and diastolic pressure following the treatment for each group will be analyzed using a paired t-test or a Wilcoxon signed rank test, and the 95% confidence interval will be presented. To assess the difference in the tendency for each visit, repeated measures analysis of variance will be performed. A significance level of 5% will be used in all analyses.

The average pulse pressure, change in the baseline blood pressure following the treatment, BMI, EQ-5D, Ankle Brachial Pressure Index(ABI index), Brachial-Ankle Pulse wave velocity(PWV index), heart rate variation (LF/HF ratio, TP, VLF, LF, HF, heart rate, SDNN, LF norm, HF norm), and blood test results will be analyzed using the same techniques used to analyze the validity of the assessment variable. To determine whether there are differences in the distribution of the change in symptoms among the groups, analysis will be performed on each item using the chi-squared test.

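### The efficacy ANCOVA omits age and sex, the two randomization factors, and gives the stratification label to hypertension stage, which was not one

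*Protocol article*

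**What the plan says.** Protocol article, Randomization: "stratified randomization will be performed by classifying subjects into age and sex by an online centralized randomization service". No other randomization factor is named there or elsewhere, and the age cut-points are not given.

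Protocol article, Statistical analysis: the efficacy ANCOVA takes "the baseline score as the covariate", "the group as the fixed factor, and the hypertension stage as the stratified variable". Age and sex are not listed. The sentence also fails to name the dependent variable. The next sentence plans to set stage-stratified results against whole-pool results "to determine whether hypertension stage is a suitable stratification variable". The same section states: "A significance level of 5% will be used in all analyses".

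On size, under Design: "Forty-five subjects with pre- or stage I hypertension will be randomized into three groups". Under Randomization: "Allowing for a 20% dropout rate, each group will include 15 participants". The aims include testing the methods and calculating the sample size for later trials.

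**The concern.** The article names both its randomization factors and its model terms, and the two lists do not match. This is therefore a conflict on the page and not a detail left to a fuller document.

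Stratified allocation balances the arms on age and sex, so these factors contribute little to the difference between arms. A model that leaves them out still counts their variance as residual error. If they are prognostic given baseline, the reported standard error then exceeds the true sampling variability of the contrast. What is at stake is precision and power in a small trial, and a variance estimate that the trial exists partly to supply.

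The stage comparison is a second, smaller matter. Similar or different results from two analyses of the same 45 people say little about whether stage would be a good stratification factor.

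**Working it through.** **The plan's own figures.** 3 × 15 = 45 agrees with the stated total. 15 × 0.8 = 12 evaluable per arm, or 36 in all. The article gives no effect size, SD or power, so 15 cannot be derived from its inputs. Nothing below depends on that.

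**Terms side by side.**

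| | Age | Sex | Baseline BP | Stage |
|---|---|---|---|---|
| Randomization | yes | yes | no | no |
| ANCOVA | no | no | yes | yes |

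**Expected size under exact balance.** These inputs are assumed, not in the documents: two age bands, each factor split 50:50, an effect of b mmHg for each, residual SD 8 mmHg (variance 64). A 50:50 binary factor with effect b has variance b²/4, so age and sex together add b²/2 to the error when omitted. The variance ratio is 1 + (b²/2)/64, and the SE ratio is its square root.

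- b = 2: 1 + 2/64 = 1.031; SE ratio 1.016
- b = 4: 1 + 8/64 = 1.125; SE ratio 1.061
- b = 8: 1 + 32/64 = 1.50; SE ratio 1.225

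**Simulation.** 45 subjects, three arms, permuted blocks of 3 within 2 × 2 age-by-sex strata, no treatment effect, week-4 systolic pressure as outcome, 4,000 runs per row. The SE ratio is model SE over empirical SE of a pairwise contrast. Type I error is for the group F-test at 5%.

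| Effect of age and of sex | Planned: SE ratio | Planned: type I | With age and sex: SE ratio | With age and sex: type I |
|---|---|---|---|---|
| 0 | 1.005 | 0.043 | 1.006 | 0.042 |
| 2 mmHg | 1.018 | 0.043 | 1.004 | 0.048 |
| 4 mmHg | 1.042 | 0.039 | 0.987 | 0.053 |
| 8 mmHg | 1.212 | 0.014 | 1.011 | 0.053 |

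Monte Carlo error is about 1/√(2 × 4000) = 1.1% on an SE ratio and √(0.05 × 0.95/4000) = 0.003 on type I error. The 2 mmHg row therefore cannot be told apart from no effect. The 8 mmHg row is clear.

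**Same question by variance explained.** If age and sex explain 10, 20 or 30% of residual variance, exact balance gives √(1/0.9) = 1.05, √(1/0.8) = 1.12 and √(1/0.7) = 1.20. With 9 of 45 lost at random after randomization, simulation puts the overstatement at about 3.5%, 8% and 13%, because dropout undoes part of the balance.

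**Carry-over to the next trial.** The residual variance from a model without age and sex is 1/(1 − R²) times the adjusted one: 1.11, 1.25 or 1.43 at R² of 10, 20 or 30%. A later trial that adjusts for both, but is sized on the unadjusted figure, would be about 11%, 25% or 43% too large.

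**Stage.** Under an assumed baseline distribution within the eligibility limits, stage correlates about 0.68 with systolic pressure. Adding it to the model moves the empirical SE from 2.941 to 2.984 (1.5%), which is nearly neutral. If half the sample is stage I (assumed), 36/(3 × 2) = 6 completers per arm per stage. By exact enumeration with 22 of 45 in stage I, the chance that some two of the three arms differ by 4 or more stage I patients is 42%. For one given pair it is about 21%.

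**The case against.** The strongest reply is that baseline blood pressure is already in the model and may absorb most of what age and sex predict. If so, the planned standard errors are right, as the zero-effect row shows. Nothing in the article says how prognostic age and sex are beyond baseline, and the larger figures need large assumed effects. Dropout shrinks them further. The error is also conservative, in a pilot that states no power. All of this stands, and it limits the severity.

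Two stronger readings are tempting. A reader might infer that the ANCOVA's standard errors are wrong outright, or that the 5% level is breached. The documents do not support this: the overstatement is conditional on prognostic strata, and no scenario raises the planned model's type I error above 5%.

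A reader might also infer that stage is redundant and should be removed. That does not follow either. The eligibility table sets limits on both systolic and diastolic pressure, so stage carries information on the other component. A baseline factor may be adjusted for without having been a randomization stratum. The article gives stage an exploratory purpose that fits a pilot testing its methods. Chance imbalance in stage is ordinary, and the baseline term deals with much of it.

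What the reply does not remove is the mismatch between the two sections, or the weakness of the stage comparison at this size.

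**Conclusion.** The point holds as a conflict between design and analysis, of moderate severity. The model omits the two factors used in randomization and gives the stratification label to one that was not used. The consequence is standard errors that are either correct or too large: about 2%, 4% and 21% too large at assumed effects of 2, 4 and 8 mmHg each, and nil if age and sex add nothing to baseline. The direction is conservative. Power is lost, the treatment estimate is unbiased, and the variance passed to the next sample-size calculation may be inflated. These sizes rest on an assumed residual SD of 8 mmHg, two age bands and blocks of 3, none of which the article gives. The case for correcting it is that the trial chose to balance age and sex, and analysing by them is nearly free. The planned stage comparison cannot settle whether stage is a suitable stratifier.

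**What to change.** In Statistical analysis, define the efficacy ANCOVA as: week-4 pressure (or change) = group + continuous baseline value of the same pressure + the age stratum and sex used in randomization. Name the outcome explicitly, once for systolic and once for diastolic pressure.

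Call hypertension stage a prespecified exploratory covariate or subgroup factor and drop the stratification label. If stage was in fact a randomization stratum, correct the Randomization section and include stage in the model on that ground.

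State that agreement or disagreement between stage-stratified and whole-pool results is descriptive only. An exploratory interaction estimate with its 95% confidence interval could be added, but that is optional and answers a different question.

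Cost: a sentence or two and a few model degrees of freedom (two if there are two age bands; the cut-points are not given). No new data are needed, since allocation already requires age and sex.

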### Ethics

This protocol adheres to the principles of the Declaration of Helsinki and has been approved by the institutional review boards of the Woo-suk University Hospital, where the study will take place (WSOH IRB 1205-02). Before any treatment is given, written consent will be obtained from each participant. All patients will have the right to withdraw from the trial at any time.

### Participants

Inclusion criteria were as follows: (1) aged between 19 and 65 years; (2) pre- or stage I hypertension (JNC 7); (3) the participants are volunteers, and written consent was obtained.

Exclusion criteria were as follows: (1) taking medications to control blood pressure; (2) secondary hypertension; (3) history of cerebrovascular disease, cardiovascular disease, malignant tumors, kidney diseases, liver diseases, thyroid gland diseases, active tuberculosis, or other infectious diseases; (4) diabetic patients taking insulin or anti-diabetic medications; (5) drug or alcohol dependence; (6) taking hemorrhagic disease and anticoagulation medications (excluding aspirin); (7) receiving systemic steroid therapy or immunosuppressive therapy; (8) taking medications that could affect blood pressure such as central nervous system depressants or stimulants; (9) pregnancy or the possibility of pregnancy; (10) hypersensitivity reactions following moxibustion therapy; (11) received oriental medicine treatment related to hypertension in the past month; (12) participants deemed unsuitable for the trial, as judged by the person in charge of the clinical trial (Table 1).

**Table 1 T1:** Patient inclusion and exclusion criteria

**Inclusion criteria**		**Exclusion criteria**	
1.	Aged between 19 and 65 years	1.	Taking medications to control blood pressure
2.	Pre- or stage 1 hypertension (JNC 7)	2.	Secondary hypertension
	-Systolic blood pressure between 120 and 159 mmHg	3.	History of cerebrovascular disease, cardiovascular disease, malignant tumors, kidney diseases, liver diseases, thyroid gland diseases, active tuberculosis, or other infectious diseases
	- Diastolic blood pressure between 80 and 99 mmHg	4.	Diabetic patients taking insulin or anti-diabetic medications
3.	The participants are volunteers and written consent obtained	5.	Drug or alcohol dependence
		6.	Taking hemorrhagic disease and anticoagulation medications (excluding aspirin)
		7.	Receiving systemic steroid therapy or immunosuppressive therapy
		8.	Taking medications that could affect blood pressure such as central nervous system depressants or stimulants
		9.	Pregnancy or the possibility of pregnancy
		10.	Hypersensitivity reactions following moxibustion therapy
		11.	Received oriental medicine treatment related to hypertension in the past month
		12.	Participants deemed unsuitable for the trial, as judged by the person in charge of the clinical trial.

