### Control group (untreated group)

The control group (untreated group) will receive no treatment. The subject in this group will be asked to maintain their normal lifestyle, including diet, exercise and workload.

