### Permitted and prohibited concomitant treatments

Brochures containing information on dietary changes, living habits, and exercise regimens that help prevent and alleviate hypertension will be distributed to all groups, and the subjects will decide for themselves whether to incorporate the suggested changes into their daily lives.

All groups will be prohibited from undergoing active treatment to lower the blood pressure for the duration of their participation in this clinical trial. After the completion of the clinical trial, during the assessment period, the subjects will be allowed to decide for themselves whether to receive additional treatment. Any other related information will be recorded in detail.

The use of birth control pills and central nervous system stimulants or depressants, which can affect blood pressure, will remain prohibited. The practitioner will be allowed to converse with the subjects about daily care and treatment details while carrying out the required examination.

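### Outside moxibustion is restricted by its indication, not by modality, so the untreated control and the two-versus-three-sessions contrast are not secured

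*Protocol article*

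**What the plan says.** Four sections of the protocol article bear on this.

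- **Participants and Table 1.** Criterion 11 excludes anyone who "received oriental medicine treatment related to hypertension in the past month". The only criterion that names moxibustion, number 10, concerns "hypersensitivity reactions following moxibustion therapy", not use. Criterion 12 leaves a discretionary exclusion for "participants deemed unsuitable for the trial, as judged by the person in charge of the clinical trial". Criterion 8 excludes people on drugs that could affect blood pressure, with no condition on why they take them.
- **Permitted and prohibited concomitant treatments.** "All groups will be prohibited from undergoing active treatment to lower the blood pressure for the duration of their participation in this clinical trial". The same section adds: "The use of birth control pills and central nervous system stimulants or depressants, which can affect blood pressure, will remain prohibited". It lets participants choose additional treatment in the later assessment period and says that other related information will be recorded.
- **Control group.** "The control group (untreated group) will receive no treatment", and its members are asked to keep to their usual lifestyle.
- **Design.** "participants will be recruited from Woo-suk University Hospital using notices at the hospital and newspaper advertisements".

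The Background names cold syndrome, deficiency conditions and chronic diseases as the typical uses of moxibustion. The primary outcome is the change in blood pressure from baseline to week 4.

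**The concern.** The two rules that reach oriental medicine turn on why it was given: for hypertension, or to lower blood pressure. The trial's hypothesis turns on what is given, namely heat at the acupoints acting on the vessels. The protocol already applies the second logic to drugs: a contraceptive pill is barred because it can affect blood pressure, although nobody takes it for that purpose. It does not apply that logic to the modality under test.

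A volunteer having moxibustion for indigestion or knee pain therefore passes criterion 11, and the on-trial rule as worded does not tell that person to stop. Such use is foreseeable, since by the Background's account moxibustion is ordinarily given for conditions other than hypertension, and part of the recruitment is by notices in the hospital that runs the trial.

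Two contrasts are at stake: moxibustion versus no treatment, and group A versus group B. The pilot's effect estimate is also intended to size future trials, so dilution here would carry forward into their design.

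**Working it through.** **1. The stated rules side by side**

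| Exposure | Stated filter | Barred whatever the reason for use? |
|---|---|---|
| Drugs affecting blood pressure (criterion 8) | effect on blood pressure | yes |
| Contraceptive pills, CNS drugs on trial | effect on blood pressure | yes |
| Oriental medicine in the past month (criterion 11) | related to hypertension | no |
| Other treatment on trial | given to lower blood pressure | no |

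Moxibustion for another complaint meets neither of the last two filters. Criterion 10 does not reach it, and criterion 12 reaches it only if the person in charge so decides.

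**2. The plan's own figure**

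The Randomization section gives 15 per group, allowing for 20% dropout. This implies 15 × 0.8 = 12 completers per group and 3 × 15 = 45 in total, which agrees with the Design section. The article gives no effect size, standard deviation or power, so 15 cannot be derived further, and it is not disputed here.

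**3. Dilution of treated versus control**

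Let k of 15 controls have outside sessions, each obtaining a fraction f of the full trial effect, with the treated arms unchanged and all 15 analysed. The expected difference shrinks by k × f / 15. A future sample size based on the diluted effect, with the standard deviation unchanged, grows by 1 / (1 − k × f / 15)².

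| k | f | Dilution | Sample-size factor |
|---|---|---|---|
| 0 | any | 0% | 1.00 |
| 1 | 1 | 6.7% | 1.15 |
| 2 | 1 | 13.3% | 1.33 |
| 3 | 1 | 20% | 1.56 |
| 1 | 0.5 | 3.3% | 1.07 |
| 3 | 0.5 | 10% | 1.23 |

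If only the 12 implied completers were analysed, one fully affected control would count for 1/12 = 8.3%. Both k and f are assumptions, because the article gives neither. The rows with f = 1 are upper bounds for their k, provided that outside sessions do no more than the trial course.

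**4. Group A versus group B**

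Group A is planned to have 2 × 4 = 8 sessions and group B 3 × 4 = 12. A group A participant with one outside session a week has 3 × 4 = 12, the planned number in group B. Whether that session would act like a study session depends on the points and technique used, which are unknown.

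**5. Use before baseline**

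This exposure precedes randomisation, so its expected share is the same in every group, and the Statistical analysis section also adjusts for the baseline value by analysis of covariance. What remains is chance imbalance and extra variability with 15 per group. The within-group paired tests have no such protection, but they are not the between-group comparison.

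**The case against.** **The article is condensed and permits nothing.** No section allows outside moxibustion, and a detailed list of concomitant treatments may sit in the full protocol. A reader might infer an outright contradiction between the untreated control and the other rules. The article does not support that, because a contradiction would need a passage allowing treatment. What stands is narrower: criterion 11 and the on-trial rule are stated, and as stated their filter misses the test modality. That is a matter of what the text fixes, not of detail left out.

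**Other text may already cover it.** The control-group sentence can be read as a restriction on controls, staff might treat study-point moxibustion as blood-pressure treatment, and criterion 12 could be used. These readings are possible. But the control sentence more naturally describes what the trial provides, and it reaches neither groups A and B nor the month before baseline. Criterion 12 sets no rule. Recording other related information describes exposure without preventing it.

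**Carry-over does not bias the comparison.** A reader might infer that recent moxibustion, by lowering baseline, biases the treatment effect. This part of the objection stands: randomisation balances such use in expectation, and the covariance analysis adjusts for baseline.

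**The size is assumed.** This stands as well. Occasional sessions elsewhere are unlikely to match five acupoints, five applications at each, and two or three sessions a week for four weeks. Recruitment also uses newspaper advertisements, and criterion 3 removes people with many chronic diseases. The standard error of a standardised difference with 15 per group is about √(2/15) = 0.37. For an assumed effect of 0.5, dilution of 6.7% to 20% is a shift of 0.03 to 0.10, well inside that noise. Even so, dilution from control use is systematic and cheap to prevent.

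**Conclusion.** The point holds as a fault in how the stated rules are framed. Criterion 11, Table 1 and the on-trial prohibition filter oriental medicine by indication, whereas the drug rules filter by effect on blood pressure. As a result, moxibustion or acupuncture for another complaint is not expressly barred before baseline or during the four treatment weeks, and neither the untreated control nor the frequency contrast is secured.

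The supportable size is a bound per person: at most 6.7% dilution for each fully affected control among 15, assuming the treated arms are unchanged, all 15 are analysed, and outside sessions do no more than the trial course. The 20% dilution and 1.56-fold sample size are what three fully affected controls would give; they are illustrations, not estimates, and the true figure could be zero. Recent use before baseline mainly adds noise. The matter deserves correction because the remedy is small, not because large contamination has been shown.

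**What to change.** - **Participants, criterion 11, and Table 1:** reword so that moxibustion or acupuncture for any indication in the past month is covered, and keep the existing wording for other hypertension-related oriental medicine.
- **Permitted and prohibited concomitant treatments, with Control group:** reconcile the two sections so that the concomitant-treatment rule expressly covers the test modality, in all three groups, up to the week-4 primary assessment.
- **Data collection:** record any outside moxibustion or acupuncture at every visit, including follow-up to week 24, so that its influence on the effect estimate used to size future trials can be examined.

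The cost is a short amendment, one screening question, one item on the visit form, and a few volunteers who become ineligible.
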